#### Functional tests

Pelvic obliquity, passive ranges of motion of the hip, knee and ankle joint and muscular flexibility of the iliopsoas muscle, rectus femoris muscle and the hamstrings are examined by a physiotherapist.

#### Isometric strength measures

The Isomed 2000 (D&R GmbH, Hernau, Germany) isokinetic dynamometer is used to measure isometric peak torque for hip abduction (HAB), hip adduction (HAD), hip flexion (HF) and hip extension (HE). The feasibility and reliability of the test protocol was evaluated in a previous study. It was shown, that HAD and HE are prone to larger measurement errors. This can be explained by a hindered fixation, as the pelvis is pried upwards when the leg pushes downwards [37]. For this reason, tests are accompanied by two investigators to ensure proper fixation and to decrease the time necessary per measurement and ensuring a high level of standardization with respect to the test procedure. While one investigator operates the device and give standardized instructions to each subject, another investigator manually stabilize the subject's pelvis during all measurements of HAD and HE, where the pelvis tends to become instable. This investigator further monitors the subjects during the measurements for signs of pain or muscle cramps.

Test procedure: Subjects accomplish a five minute warm-up on a bicycle ergometer (50-100 Watt) followed by some stretching exercises. Subsequently, the randomly selected starting leg is allotted and subjects remove their shoes. Prior to the test, a knee orthosis is attached to the tested leg. For HAB and HAD, the orthosis is set at 90° at the knee. For HF and HE, the orthosis is set at 0°. The orthosis is necessary to decrease measurement artifacts related to oscillations and resulting moments of inertia of the shank and foot. All test modes are performed on each leg separately. Test mode and sequence, subject positioning, joint angle position and annotations for fixation are given in Table 4. Maximal axis-joint alignment is insured before subjects are fixed to the surface and dynamometer. Each trial is initialised by a sub-maximum test trial to allow participants to get used to the work movement and measurement procedure. Participants are then asked to contract their muscles to the maximum three times in a given time frame of 40 seconds against the fixed lever arm of the dynamometer. Each test trial is followed by a break of 30 seconds. After all strength tests, a physiotherapist performs some traction and stretching exercises to allow relaxation of joints and muscles of the participants.

**Table 4 T4:** Test modalities for isometric strength measures.

Test mode and sequence	Position and fixation	Joint angle
**1. Hip abduction (HAB)**	• Recovery position (lateral) • Belts strapped around pelvis and contra-lateral leg	• 0°
		
**2. Hip adduction (HAD)**	• lower arm on the pillow, upper arm grasps the edge of the examination table • Tested leg in 90° knee flexion, fixed with orthosis	• 20° abduction
		
**3. Hip flexion (HF)**	• Supine position • Belts strapped around pelvis and contra-lateral leg	• 20° flexion
		
**4. Hip extension (HE)**	• Arms are folded • Tested leg in 0° knee flexion, fixed with orthosis	• 60° flexion

### Proposed sample size/power calculation

The primary endpoint is the change of SF36: Subscale bodily pain from M1 to M2 of HS in comparison to CO. Responsiveness of the subscale is comparable to the pain scale of the disease specific WOMAC in patients with osteoarthritis undergoing a rehabilitation intervention [52]. The SF36 is recommended as a generic instrument for recording relevant domains in osteoarthritis of the lower limb [53]. It is the most widely used generic health instrument [52] and allows comparison of disease states within and between different disorders.

Sample size calculation is based on clinically relevant changes: An effect smaller than the minimum clinical important difference (MCID) may be measureable although patients will be unable to notice it [50]. MCID was derived from literature [50], basic values and statistical spread of the measure for the given population were derived from a pilot study of our own research group on subjects with hip osteoarthritis. According to the mentioned presumptions, a sample size of n = 60 in each group will have 80% power to detect a clinically relevant difference in bodily pain for HS in comparison to CO using a two group t-test with a 0.05 two-side significance level. A failure rate of 15-20% is approximated, thus final sample size is set at n = 70 for each group, except US with n = 7. This is only an explorative intervention. Sample size was calculated using G*Power Version 3.0.10 (Franz Faul, Universitaet Kiel, Germany).

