## Methods/Design

### Design

This is a randomized, controlled trial, single-blinded for participants for two of the four treatment options (sham ultrasound and ultrasound) (Figure 1). Recruited patients undergo telephone screening followed by a clinical examination by a medical doctor to ensure eligibility. Eligible participants then undergo outcome assessment using the complete test battery prior to intervention, and will subsequently be randomized to one of the four groups. A ratio of 10:10:10:1 will be used for randomization into Hip School (HS), no intervention group (CO), sham ultrasound group (SUS), and ultrasound group (US). During the 12 week intervention period, monthly logbooks for physical exercises and pain have to be completed by all subjects. The complete test battery is repeated after the 12 week interventional period. Questionnaires (WOMAC, SF36) and log books are accessed via telephone assessment 16 and 40 weeks after the retest.

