### Statistical analysis

Data will be analyzed on an intention-to-treat principle using all randomized participants. Missing data will be filled in by carrying the last score forward. A per protocol analysis will also be conducted as a subordinate type of analysis. Demographic characteristics, joint and muscle function, and logbooks will be displayed with descriptive statistics. Multivariate statistics will be used (factors: group × time) for outcomes measured on a continuous scale. For strength measures, baseline levels will be included as covariates.

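### Seventy per group covers about 14% loss, not the full 15-20% failure rate it is said to allow for; at 20% loss, power is about 77-78%

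*Protocol article*

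**What the plan says.** All the sample size figures stand together in the protocol article, under Proposed sample size/power calculation.

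- **Comparison.** "The primary endpoint is the change of SF36: Subscale bodily pain from M1 to M2 of HS in comparison to CO".
- **Requirement.** "a sample size of n = 60 in each group will have 80% power to detect a clinically relevant difference in bodily pain", "using a two group t-test with a 0.05 two-side significance level".
- **Source of the effect size.** "MCID was derived from literature [50], basic values and statistical spread of the measure for the given population were derived from a pilot study". Neither the MCID nor the spread is printed.
- **Allowance for loss.** "A failure rate of 15-20% is approximated, thus final sample size is set at n = 70 for each group".

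Under Design, Hip School and the no-intervention group are allocated in equal numbers (both have 10 in the 10:10:10:1 ratio). Under Statistical analysis, the main analysis set is everyone randomised: "Data will be analyzed on an intention-to-treat principle using all randomized participants". For missing values: "Missing data will be filled in by carrying the last score forward".

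**The concern.** The protocol presents 70 as the consequence of a requirement of 60 and an expected failure rate of 15-20%. To keep 60 after a proportion r is lost, a trial must recruit 60/(1 − r), and that exceeds 70 throughout the stated range. Multiplying instead, 60 × 1.15 to 60 × 1.20, gives 69 to 72. This would explain the choice of 70, but it is only an inference about how the figure arose.

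At stake is the power of the single primary comparison. The article's background motivates the trial by the lack of adequately powered studies in hip osteoarthritis, so the stated power should follow from the stated inputs.

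**Working it through.** **Inputs.** From the sample size section: 60 per group, 80% power, two-sided α = 0.05, two-group t-test, failure rate 15-20%, 70 recruited per group. The standardised difference d is not given and has to be back-solved.

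**Step 1: the plan's own figure.** The 60 cannot be derived independently without the MCID and SD. With the exact (noncentral t) calculation, n = 60 per group gives 80.0% power when d = 0.5157. Sample size programs round up, so any d up to about 0.5201 (the value at which 59 per group would be just enough) also leads to 60. Both ends are carried through below.

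**Step 2: recruits needed to keep 60, as 60/(1 − r), and patients left from 70, as 70 × (1 − r).**

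| Loss r | Needed per group | Left from 70 |
|---|---|---|
| 15% | 60/0.85 = 70.6, so 71 | 59.5 |
| 17.5% | 60/0.825 = 72.7, so 73 | 57.75 |
| 20% | 60/0.80 = 75 | 56 |

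Break-even loss: 1 − 60/70 = 14.3%.

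**Step 3: power among completers (two-sided t-test, α = 0.05).**

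| Loss | n per group | d = 0.5157 | d = 0.5201 |
|---|---|---|---|
| 15% | 59.5 | 79.7% | 80.3% |
| 17.5% | 57.75 | 78.5% | 79.1% |
| 20% | 56 | 77.2% | 77.9% |

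**Step 4: all 70 analysed with the last score carried forward.** If the effect were undiluted, 70 per group would give 85.8% power at d = 0.5157. However, the SF36 is collected at M1, M2 and the two later telephone contacts, and the monthly logbooks between M1 and M2 do not contain it. A participant without an M2 score therefore has M1 carried forward, and the M1-M2 change is zero.

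Assume also equal loss r in both arms and no mean change in controls. With q = 1 − r and the completers' SD set to 1:

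- mean difference = q × d
- variance in Hip School = q(1 + d²) − (qd)²
- variance in controls = q
- effective standardised difference = qd / √(average of the two variances)

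For d = 0.5157:

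- r = 15%: difference 0.438; variances 0.884 and 0.850; pooled SD 0.931; effective difference 0.471; power 79.0%.
- r = 20%: difference 0.413; variances 0.843 and 0.800; pooled SD 0.906; effective difference 0.455; power 76.3%.

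At d = 0.5201 the same formulas give 79.6% and 76.9%.

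**The case against.** Four fair points can be made for the plan.

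1. **The failure rate is only approximate, and at its lower end 70 is good enough.** This stands. At 15% the gap is half a patient per group (71 recruits against 70), and power lies between 79.7% and 80.3% depending on how 60 was rounded. A reader might infer that 80% power is missed materially across the whole range. The documents do not support that.

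2. **The 80% is stated for 60 per group, not for 70 recruits after 20% loss.** This also stands: the power sentence itself is not shown to be wrong. What fails is the step from 60 and 15-20% to 70.

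3. **The main analysis keeps all 70 per group, so the analysed number never falls to 56.** True of the number, but it does not settle the power. The 85.8% requires an undiluted effect, and a carried-forward M1 score dilutes it. The figures of 79% and 76% in turn rest on equal loss in both arms and unchanged controls, which the protocol does not state. The protocol also does not define failure: participants who stop the programme but still attend M2 would have observed scores. So the carried-forward analysis may do better or worse than these figures, and it cannot be relied on to restore 80%.

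4. **Baseline adjustment could recover the lost power.** The statistical analysis section names baseline covariates only for the strength measures, and bodily pain falls under the general group × time analysis. A power figure for an adjusted analysis of pain would describe something the article does not specify.

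**Conclusion.** The point holds in a limited form. As written, 70 per group is not the result of allowing for 15-20% failure on 60: it covers about 14% loss. At 15% the aim is essentially met. Towards 20% it is not: 56 per group remain, 4 fewer than required, and completer power is about 77-78%, roughly 2 to 3 points below 80%. Keeping 60 at that loss would take 75 recruits per group, 5 more than planned.

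Every power figure depends on the back-solved standardised difference of about 0.516-0.520; the carried-forward figures also depend on the assumptions in the working. The counts (59.5, 56, 71, 75 and the 14.3% break-even) depend on none of these. The shortfall is small and does not invalidate the design, but the stated allowance is wrong at the upper end of its own range.

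**What to change.** Keep 70 per group and replace the sentence on the allowance with one to this effect: seventy per group gives 80% power for the Hip School versus no-intervention comparison with up to about 14% loss, and about 77% at 20% loss (unadjusted two-group t-test). Printing the MCID and SD behind the 60 would let readers check these figures without back-solving.

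Do not restate power for a baseline-adjusted analysis unless that adjustment is first specified for bodily pain.

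The cost is one sentence and a slightly less favourable power statement. No extra recruitment or change of analysis is needed. If the sponsor would rather keep the claim that 60 remain at 20% loss, the price is 75 per group.

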### Statistical analysis

Data will be analyzed on an intention-to-treat principle using all randomized participants. Missing data will be filled in by carrying the last score forward. A per protocol analysis will also be conducted as a subordinate type of analysis. Demographic characteristics, joint and muscle function, and logbooks will be displayed with descriptive statistics. Multivariate statistics will be used (factors: group × time) for outcomes measured on a continuous scale. For strength measures, baseline levels will be included as covariates.

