### Study purpose

The primary aim of this study is to determine whether a 12-week intervention program comprising group and home-based exercises decreases bodily pain in subjects with hip osteoarthritis in comparison to a non-treated control group. Efficacy is quantified by the subscale *bodily pain *of the SF36. The secondary aim is to determine whether this exercise regime can improve function, health-related quality of life, strength of hip surrounding muscles, postural control in bi-pedaled, tandem-, and single leg stance, joint function, and gait parameters in comparison to a non-treated control group, an attention control group (sham ultrasound), and an ultrasound group. Ultrasound therapy is only investigated in an explorative manner. Follow-up data are recorded to evaluate the sustainability of the interventional programs over another 40 weeks.

It is hypothesized that a 12-week intervention program will (1) decrease pain, and (2) improve physical function in comparison to a non-treated control. It is further hypothesized that (3) the efficacy of the exercise regime is superior to the efficacy of an intervention solely aiming for attention control, and (4) that effects are long-acting.

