### Outcome measures (Figure 1)

Participants are assessed at baseline (M1), and 12 weeks after the intervention period (M2). Patient characteristics (age, gender, height, weight) are evaluated at the baseline assessment. Questionnaires (WOMAC, SF36), measures of postural control, clinical gait analysis, functional tests (passive range of motion (ROM), muscle flexibility), and isometric strength measures are evaluated at M1 and M2. Previous physiotherapy and/or exercises, medication, and pain (retrospective time frame of four weeks) are evaluated at M1 and noted each subsequent month up to M2 in a logbook. Satisfaction with the therapy regime is assessed with a questionnaire at M2 and M3. 16 weeks past M2 (M3) and 24 weeks past M3 (M4), participants are contacted again via telephone to assess WOMAC, SF36, previous physiotherapy and/or exercises, and medication.

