#### Monthly logbooks

Participants are asked to fill out a monthly logbook between M1 and M2. They have to specify previous physiotherapy and/or exercise, medication, and pain (retrospective time frame of four weeks). This information is also requested on M3 and M4 in the context of the telephone call.

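### Carrying the last score forward enters every participant missing at M2 as exactly zero change in bodily pain, which biases the primary estimate, and it can overstate durability at M3/M4 if a benefit wanes

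*Protocol article*

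**What the plan says.** The section Statistical analysis sets both the analysis set and the missing-data rule: "Data will be analyzed on an intention-to-treat principle using all randomized participants", and "Missing data will be filled in by carrying the last score forward". The only other analysis named is per protocol: "A per protocol analysis will also be conducted as a subordinate type of analysis". That changes who is analysed; it does not vary the assumption about missing scores in the randomised set.

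The section Proposed sample size/power calculation defines the endpoint, "The primary endpoint is the change of SF36: Subscale bodily pain from M1 to M2 of HS in comparison to CO", and gives the expected loss: "A failure rate of 15-20% is approximated". The section Outcome measures lists the tests done around the intervention, beginning with the WOMAC and SF36 questionnaires, and ends that list with "isometric strength measures are evaluated at M1 and M2". The SF36 is then repeated by telephone at M3 (16 weeks after M2) and M4 (24 weeks after M3). Between M1 and M2 the only pain data come from a different instrument: "Participants are asked to fill out a monthly logbook between M1 and M2". The last of the hypotheses in Study purpose is "and (4) that effects are long-acting".

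**The concern.** With one SF36 score before M2, carrying the last score forward is the same as carrying baseline forward. A missing M2 becomes a change of zero, in every arm and whatever the reason for leaving. This is right on average only if dropouts' true mean change is zero, or if the errors in the two arms cancel. The filled-in scores are then analysed as if they had been measured.

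What is at stake first is the primary estimate. The trial is sized on a minimum clinically important difference, so a true effect at that threshold could be reported clearly below it. Under other dropout patterns a difference could appear where none exists. Second is the hypothesis of lasting effects: for someone lost after M2, the rule supplies the persistence that the follow-up is meant to test.

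**Working it through.** **Inputs from the protocol article.** 60 per arm, 80% power, two-group t-test, two-sided 0.05; 70 per arm randomised; 15-20% failure; HS and CO allocated 1:1.

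**Assumed, because the article gives no figures.** SD of the M1-M2 change = 1; positive change = improvement; dropout by arm; mean changes; losses after M2.

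**1. The planned effect.** The clinically important difference and SD are not printed, so n = 60 cannot be reproduced independently. Solving the noncentral t-test for n = 60 per arm and 80% power gives a standardised difference d = 0.516.

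**2. Number imputed.** 0.15 × 70 = 10.5 and 0.20 × 70 = 14 per arm.

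**3. General form at M2.** With dropout f and true mean change μ in an arm, and dropouts like completers:
- recorded mean = (1 − f)μ
- recorded variance = (1 − f) + f(1 − f)μ²

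**4. Equal dropout, CO change 0, HS change d.** The expected difference is (1 − f)d.

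| f | Expected difference | Share of true | Power, rule, 70 per arm | Power, observed M2 only |
|---|---|---|---|---|
| 0.15 | 0.438 | 85% | 79.0% | 79.7% (59.5 per arm) |
| 0.20 | 0.413 | 80% | 76.3% | 77.2% (56 per arm) |

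The rule itself costs 0.7 or 0.9 percentage points of power. Under this assumption the observed-score analysis is unbiased.

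**5. Standard error at f = 0.20.** The variances are 0.8 + 0.16 × 0.516² = 0.843 (HS) and 0.800 (CO), so SE = √(1.643/70) = 0.153. Had all 70 per arm been measured, it would be √(2/70) = 0.169; with 56 observed, √(2/56) = 0.189. The rule reports more precision than complete data would have given.

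**6. Unequal dropout, no true effect.** Assume 30% in HS and 10% in CO, with both arms worsening by 0.5 SD. The difference is 0.7 × (−0.5) − 0.9 × (−0.5) = +0.10 SD in favour of HS. The variances are 0.7525 and 0.9225, and the 5% test rejects in about 9.8% of trials. If both arms improve by 0.5 SD, the sign reverses. With equal dropout the difference is 0 and the error rate stays at 5%.

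**7. M4.** Let r be the share of the M2 benefit truly remaining and g the share lost after M2, with everyone seen at M2. The share shown is (1 − g)r + g.
- r = 0, g = 0.20: 20% shown, a false residual of 0.20 × 0.516 = 0.10 SD. The 5% test rejects in 9.3% of trials (70 per arm, unit SD as an approximation).
- r = 0, g = 0.30 or 0.40: 0.15 or 0.21 SD; rejection 14.9% or 22.8%.
- r = 0.5, g = 0.20: 60% shown.
- r = 1: 100% shown, no bias.
- r = 1.5, g = 0.20: 0.8 × 1.5 + 0.2 = 140% shown, an understatement.

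If 20% are also missing from M2 onwards, they are held at baseline. With r = 0.5 and g = 0.20 the share shown at M4 is 0.6 × 0.5 + 0.2 = 50%, which equals the truth because the two errors cancel.

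**The case against.** A reader might infer that the rule codes every M3/M4 dropout as a lasting benefit, or that it always favours long-acting effects. The documents do not support that. The rule freezes whatever score came last, in all arms. Someone missing since M2 stays at baseline, someone unchanged or worse at M2 stays so, and CO participants are frozen too. Overstated durability needs an M2 benefit that later wanes among people lost after M2. The M4 figures also rest on assumed losses, and the 0.10-0.21 SD residuals on complete loss of benefit. Separately, the section Interventions offers participants the other intervention for 12 weeks after M2, so M3/M4 contrasts between arms are confounded however missing scores are handled.

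A reader might also blame the rule for the shortfall from 80% power. Nearly all of it comes from dropout itself: 70 per arm covers a loss of 1 − 60/70 = 14.3%.

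Third, with similar dropout in both arms and dropouts like completers, the error is dilution and no false positive arises. Inflated type I error needs unequal dropout together with change over time, and the article gives figures for neither. It is plausible, since HS asks for three sessions a week and CO for none, but it remains an assumption.

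Fourth, missing-at-random imputation is not automatically better. If 20% of HS left with a true change of −0.5 SD and CO had no offsetting error, the rule overstates HS by 0.2 × 0.5 = 0.10 SD. Giving those dropouts the completer mean overstates it by 0.2 × (0.516 + 0.5) = 0.20 SD. Logbook pain might narrow this if dropouts kept completing it, which is not known. This stands, and it is why a sensitivity analysis must accompany the replacement.

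Finally, sensitivity analyses are commonly left to an analysis plan that is not shown, and their absence here is no fault. The point concerns the primary rule, which the article does fix.

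**Conclusion.** The concern holds in a limited form. The article commits the primary analysis to single imputation that sets every missing M1-M2 change to zero. At the article's own loss rate, and if dropouts resemble completers, the HS-CO estimate is 15-20% too small, at a power cost of under 1 percentage point compared with observed scores. The damage is a biased estimate with an overstated precision. With unequal dropout and a common drift the bias can take either sign; the 0.10 SD and 9.8% figures illustrate this under assumed inputs and are no forecast. For the hypothesis of lasting effects, the rule overstates durability on average when an M2 benefit wanes among people lost after M2. It does not do so for people already missing at M2, or if the benefit holds or grows. All SD-scale results rest on d = 0.516, back-solved from the planned sample size.

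**What to change.** Replace the sentence in Statistical analysis.

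- **M2, primary analysis.** Include all randomised participants. Handle missing bodily pain by multiple imputation within arm, using baseline bodily pain, gender, interventional period and monthly logbook pain, or by a likelihood-based mixed model on the observed scores. State the missing-at-random assumption.
- **Sensitivity.** Pair it with a delta-adjusted or reference-based analysis that lets dropouts, separately by arm, do worse than completers. Report how far the assumption must move before the conclusion changes.
- **M3/M4.** Do not carry M2 forward; use mixed models on observed data. The confounding from the treatment offer after M2 remains and needs its own handling.
- **Last score forward.** Keep it at most as a labelled sensitivity analysis.

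The cost is revised wording and modest extra programming. All the variables named are already collected, and no further participants are needed.

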**Methods/Design:**

217 participants with hip OA, confirmed using the clinical score of the American College of Rheumatology, are recruited from the community and randomly allocated to one of the following groups: (1) exercise regime "Hip School", n = 70; (2) Non-intervention control group, n = 70; (3) "Sham" ultrasound group, n = 70; (4) Ultrasound group, n = 7. The exercise regime combines group exercises (1/week, 60-90') and home-based exercises (2/week, 30-40'). Sham ultrasound and ultrasound are given once a week, 15'. Measures are taken directly prior to (M1) and after (M2) the 12-week intervention period. Two follow-ups are conducted by phone 16 and 40 weeks after the intervention period. The primary outcome measure is the change in the subscale *bodily pain *of the SF36 from M1 to M2. Secondary outcomes comprise the WOMAC score, SF36, isometric strength of hip muscles, spatial-temporal and discrete measures derived from clinical gait analysis, and the length of the centre of force path in different standing tasks. An intension-to-treat analysis will be performed using multivariate statistics (group × time).

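### The analysis section gives one unrestricted group × time analysis and never names the Hip School versus no-intervention contrast that defines and sizes the primary endpoint

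*Protocol article*

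**What the plan says.** Two sections fix the primary comparison. Study purpose asks whether the programme "decreases bodily pain in subjects with hip osteoarthritis in comparison to a non-treated control group". Proposed sample size/power calculation says: "The primary endpoint is the change of SF36: Subscale bodily pain from M1 to M2 of HS in comparison to CO". It then sizes that comparison: "a sample size of n = 60 in each group will have 80% power to detect a clinically relevant difference in bodily pain", "using a two group t-test with a 0.05 two-side significance level". The two inputs to that calculation are described but not given as numbers: "MCID was derived from literature [50], basic values and statistical spread of the measure for the given population were derived from a pilot study".

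Statistical analysis says that the intention-to-treat analysis covers all who were randomised, with the last score carried forward, and then gives one method: "Multivariate statistics will be used (factors: group × time) for outcomes measured on a continuous scale". The abstract repeats it. The section does not mention the t-test, an HS-CO contrast or any separate handling of bodily pain. It does not say how many levels group or time has. Baseline is named as a covariate for strength measures only.

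The Design section randomises 10:10:10:1 to HS, CO, SUS and US. On the last arm, Study purpose says: "Ultrasound therapy is only investigated in an explorative manner".

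**The concern.** The sample size section and the analysis section do not describe the same test. With four randomised arms, everyone analysed and an unrestricted group factor, group × time on M1 and M2 has 3 numerator degrees of freedom. It asks whether any arm's change differs from any other's. The primary question concerns one pair.

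Two things are at stake:

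- **Interpretation.** A significant interaction could come from sham differing from the rest while HS does no better than CO. A non-significant one could hide a real HS effect.
- **Pre-specification.** With group levels, time levels and the contrast all open in the published text, that text does not settle which p-value is primary.

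**Working it through.** **Inputs from the protocol article.** 60 evaluable per large arm, 80% power, two-sided 0.05, two-group t-test; enrolled 70/70/70/7 (Proposed sample size/power calculation). All randomised participants analysed (Statistical analysis).

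**Assumptions.** The minimum clinically important difference and the SD are not given as figures, so n = 60 cannot be reproduced independently. The standardised difference d is therefore solved backwards. The SUS and US effects are assumed and varied. The evaluable split 60/60/60/6 applies the 10:10:10:1 ratio to 60 per large arm.

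**Step 1: implied d.** For a two-group t-test with n per group, the noncentrality is d√(n/2) on 2n − 2 df. With n = 60, 118 df and critical t = 1.980, 80% power needs d√30 = 2.825, so d = 0.516. Feeding this back returns n = 60, which is circular and confirms nothing about the clinical inputs.

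**Step 2: where the two sections would agree.** With only HS and CO and only M1 and M2, the group × time F is the square of the t statistic on change scores. Its power is the same 80.0%.

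**Step 3: four-arm interaction, M1 and M2 only.** This is a one-way F test on change scores with 3 and N − 4 df. In SD units its noncentrality is λ = Σ nᵢ(μᵢ − μ̄)², where μ̄ is the mean weighted by nᵢ.

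Worked case at 60/60/60/6, with SUS and US halfway between CO and HS:
- μ = (d, 0, 0.5d, 0.5d), so μ̄ = 0.5d
- λ = 60(0.5d)² + 60(0.5d)² = 30d² = 7.98
- F critical (3, 182 df) = 2.65; power 64%

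Case with SUS and US equal to CO:
- μ̄ = 60d/186 = 0.323d
- λ = 60(0.677d)² + 126(0.323d)² = 40.6d² = 10.8; power 79%

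| SUS and US effect, as a share of the HS effect | 60/60/60/6 | 70/70/70/7 |
|---|---|---|
| 0 or 100% | 79% | 85% |
| 25% or 75% | 68% | 76% |
| 50% | 64% | 72% |
| SUS 0, US 100% (or the reverse) | 81% | 87% |
| **HS-CO contrast in the four-arm model** | **80%** | **86%** |

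The contrast row uses noncentrality d√(n/2) on N − 4 df: 2.825 on 182 df gives 80.2%, and 3.051 on 213 df gives 85.9%. The right-hand column assumes that carrying scores forward leaves d unchanged.

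**Step 4: rejection when the primary hypothesis is false.** Set HS = CO at 60/60/60/6:
- SUS and US both shifted by d: λ = 11.3; rejection 81%
- SUS alone shifted by d: λ = 10.8; rejection 79%
- US alone shifted by d: λ = 1.54; rejection 15%

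**Step 5: which row is relevant.** Interventions states that placebo outperforms no treatment, and the third hypothesis in Study purpose puts exercise above attention control. The article itself therefore expects sham to lie between CO and HS, where the loss is greatest, without saying how far along.

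**The case against.** The strongest reply is that the primary comparison is already fixed. The sample size section names the endpoint, window, pair of arms, test and alpha. The analysis section is one generic sentence for all continuous outcomes, and a condensed article may leave the contrast to a full plan that is not shown. Group × time is compatible with the endpoint, since restricted to HS and CO at M1 and M2 it is the powered test.

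Much of this stands, and it rules out several stronger readings:

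- A reader might infer that the protocol declares a four-arm omnibus test as primary. It does not. The four-arm reading is inferred from the analysis of all randomised participants and an unrestricted group factor.
- A reader might infer that group × time cannot test the primary hypothesis. It can, if restricted or followed by a named contrast.
- A reader might infer that M3 and M4, when participants may have moved to another intervention, enter the primary test. Abstract and sample size section both limit the endpoint to M1 to M2.
- A reader might take d = 0.516 as a planned effect or conclude that the trial is underpowered. The figure is back-solved, and omnibus power at 70/70/70/7 runs from 72% to 87%, on both sides of 80%.

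What the reply does not remove is the mismatch in the published text. The only analysis stated carries none of the restrictions that would make it the powered test.

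**Conclusion.** The point holds as a mismatch between two sections. The analysis stated does not carry through the HS-CO comparison that the preceding section defines and sizes. Taken literally it is a 3-df test of a different hypothesis. Its illustrative power is about 64% to 81% at 60/60/60/6, against 80% for the contrast, and it rejects about 79% to 81% of the time when HS equals CO but sham, with or without ultrasound, shifts by d. The power loss is negligible if sham matches CO or HS and material if it lies between them. The interpretive problem does not depend on where sham lies between CO and HS. All power figures rest on the back-solved d, the assumed SUS and US effects, and equal variances of change across arms. This should be corrected, but it is not evidence that the trial's size is wrong.

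**What to change.** In Statistical analysis, state that:

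- The primary test is the single HS-minus-CO contrast in M1 to M2 bodily pain, two-sided 0.05 with a 95% confidence interval, adjusted for baseline bodily pain. With baseline as a covariate, the arm effect is the same whether the response is the M2 score or the change, so the endpoint stays as defined.
- HS-SUS is a named secondary contrast, matching the third hypothesis.
- US is reported as exploratory and descriptive, consistent with its stated role.
- Any omnibus group × time test is supportive only.

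The cost is wording. Baseline bodily pain is already collected, no extra participants or visits are needed, and the contrast keeps the planned power (80.2% within a four-arm model at 60/60/60/6, under the back-solved d and before any gain from baseline adjustment).
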